**Trial procedure**

1. Literature review for relevant studies.
2. Drafting trial protocol and design case record form for ethical committee approval.
3. Plan for education for standard postpartum care and breastfeeding to women aged

15 to 41 years who deliver via cesarean section at 28 to 42 weeks’ gestational age at Sunpasithiprasong Hospital, Ubon Ratchathani, Thailand during February 2017 to

September 2017 and provide written informed consent.

1. Recruiting participants according to inclusion and exclusion criteria by placing advertisements in four obstetrics wards.
2. Giving trial information to potential participants using obstetrician and nurse in each obstetric ward and participant information sheet to confirm participant understanding of trial objective, procedure, benefits, and risks. If potential participants are willing to participate in trial, they will be asked to sign informed consent form with understanding that they can quit from trial at any time without any consequence.
3. Participants will be randomly assigned into three groups based on numbers generated by a table of random numbers in blocks of three: 1) Wang Nam Yen herbal tea and placebo tablet (T group), 2) domperidone tablet and placebo herbal tea (D group), 3) placebo tablet and placebo herbal tea (C group).
4. All study interventions will be prepacked and sealed in opaque packages, for three consecutive days of postpartum use. Participants and investigators were blinded to the treatment assignment. Randomization ID will be TD001 to TD120.
5. Wang Nam Yen herbal tea will be manufactured by Wang Nam Yen hospital, a community hospital in Sa Kaeo reputed for Thai traditional herbal medicine. Each Wang Nam Yen herbal tea contains sappan (*Caesalpinia sappan* Linn.) 500 mg, licorice (*Glycyrrhiza glabra* Linn.) 500 mg, bale fruit (*Aegle marmelos* L. Corr) 500 mg, ginger (*Zingiber officinale* Roscoe) 500 mg, and jewel vine (*Glycyrrhiza glabra* Linn.) 500 mg. Wang Nam Yen herbal tea will be packed in tea bag (2500 mg) designed for each meal. The herbal tea placebo will be prepared as tea bag for each meal, and the placebo tea bag will be identical with Wang Nam Yen tea bag. Both herbal teas will be prepared by diffusion in 200 mL of warm water for 5 minutes. Interventions will be administered orally three times per day after meals. The first administration will occur 12-18 hours following delivery to ensure sufficient time for the evaluation of any postpartum complications that may have occurred. Domperidone will be administered at 10 mg per dose, as 30 mg of domperidone per day are considered safe and sufficient for increasing breast milk production. Placebo tablets are identical to appearance of domperidone tablet. All participants (T, D, C groups) will be administered 200 mL of tea and a tablet after each meal.

T– The Wang Nam Yen herbal tea treatment group will receive Wang Nam Yen herbal tea and placebo tablet after each meal for three meals per day. This is an intervention arm which is designed to assess the efficacy of Wang Nam Yen herbal tea.

D– The domperidone treatment group will receive herbal tea placebo and a 10 mg domperidone tablet after each meal for three meals per day. This is an active control arm which is designed to be comparator as standard treatment.
C– The placebo control group will receive both herbal tea placebo and a placebo tablet after each meal for three meals per day. This is a placebo control arm which is designed to be a reference group with no treatment.

1. Demographic data will be recorded including age, occupation, monthly income, method of health payment, highest education. Obstetric data will be recorded including gestational age, numbers of pregnancy, numbers of delivery, numbers of antenatal visits for this pregnancy, presence of labor symptoms, indication of cesarean delivery, experience of breast feeding, nurturing environment, baby birthweight, sex of baby, immediate postpartum complication, fluid intake and output, and neonatal complication.
2. Participants will be asked to collect breast milk after received intervention at 24-72 hours postpartum using automated electric breast pump brand spectra type spectra 2 which has minimal pressure at 10 mmHg and maximum pressure at 300 mmHg. Pump cycle is approximately 42 times per minute. Breast pump will be 2 hours after last breastfeeding and pump for 15 minutes each breast. Breast milk will be recorded as milliliters (ml).
3. Drug adverse events including dry mouth, headache, insomnia, abdominal pain, diarrhea, nausea and urinary retention will be recorded.
4. Fluid intake and output will be recorded. Numbers of breastfeeding per day will be recorded.
5. Changes of bodyweight of mother and neonate will be recorded.
6. Before discharge, participants will be recorded for vital signs, fundal height, lochia color, postpartum complication, neonatal complication and participant satisfaction.
7. Collected data will be analyzed.
8. Result will be reported as standard format.
9. Conclusion, discussion and manuscript preparation.

**Statistical analysis**

The statistical analysis will be performed on an intention-to-treat basis using Stata/MP software version 15.0 (StataCorp 2017, College Station, TX). Descriptive statistics will be carried out using mean with standard deviation for normal distributed continuous data, and median with interquartile range for non-normal distributed continuous data. Categorical data will be presented as counts and percentage and will be tested for significance with Chi-square test. Continuous data will be assessed for normal distribution using histogram and Shapiro–Wilk test. One-way ANOVA with Bonferroni correction will be used for normal distributed continuous data and Kruskall-Wallis test will be used for non-normal distributed continuous data. Significant level is defined as *p*<0.05.

**Figure 3.** Trial procedure

Placing advertisements in four obstetrics wards

Recruiting participant eligible for inclusion and exclusion criteria

Obtaining informed consent from participants

Randomization into 3 groups

| T (n=40)  Wang Nam Yen herbal tea and placebo tablet | D (n=40)  herbal tea placebo and domperidone tablet | C (n=40)  herbal tea placebo and a placebo tablet |
| --- | --- | --- |

Recording baseline data and first administration of intervention at 12-18 hours postpartum

Recording fluid intake and output, numbers of breastfeeding per day, breast milk volume and
drug adverse events at 24, 48 and 72 hours postpartum

Recording primary and secondary outcomes at 72 hours postpartum

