**Sample size calculation**

We use mean and standard deviation of breast milk volume at day 4 after delivery based on the study by based on the study by Jantarasaengaram and Sreewapaon^10^ the effects of domperidone compared to placebo in augmenting lactation following cesarean delivery with 80% power and a 2-sided type I error at 5%

Mean daily milk volume in the domperidone group day 4= 191.3(SD=136.1)

Mean daily milk volume in the placebo group day4 = 91.4 (SD=60.3)

n/group = $\frac{3{(Z\alpha+Z\beta)}^{2}\delta^{2}}{\left( \mu_{1}-\mu_{2} \right)^{2}}$

$\delta=SD of primary outcome$

$$\mu_{1}=191.3 (case group)$$

$$\mu_{2} =91.4 (control group)$$

Consider α = 0.05, Zα = 1.65 Power = 80% Zβ = 0.84

n/group = $\frac{3\left( 1.65+0.84 \right)^{2}{(136.1)}^{2}}{{(191.3-91.4)}^{2}}$

Resulted in n/group = 34.52

With considering an expected follow-up loss of 15%, the anticipated sample size of 120 which would require a sample size of 40 in each group.

1. T– The Wang Nam Yen herbal tea treatment group

2. D– The domperidone treatment group

3. C– The placebo control group

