**Randomization**

Participants will be random allocated into 3 groups with 1 : 1 : 1 ratio by block randomization with block of three using table of random numbers for creating randomization ID which will be enveloped in opaque envelop to mask clinicians, data collectors and patients.

Randomization ID will be assigned as

A = T– The Wang Nam Yen herbal tea treatment group which will receive Wang Nam Yen herbal tea and placebo tablet after each meal for three meals per day.

B = D– The domperidone treatment group which will receive herbal tea placebo and a 10 mg domperidone tablet after each meal for three meals per day.

C = C– The placebo control group which will recieve both herbal tea placebo and a placebo tablet after each meal for three meals per day.

There will be 6 possible blocks of three including 1 = ABC, 2 = ACB, 3 = BAC, 4 = BCA, 5 = CAB และ 6 = CBA

When 120 randomization ID are generated, the ID will be joined together starting with randomization ID for participant number 9 (TD009) as the first ID.

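### If milk volume is judged normal, the planned ANOVA with Bonferroni pools one variance although the protocol's planning SDs are 136.1 and 60.3, which misstates the standard error of each tea comparison

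*Protocol*

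**What the plan says.** The Statistical analysis section of the protocol sorts continuous outcomes by a histogram and a Shapiro-Wilk test. For those that pass, "One-way ANOVA with Bonferroni correction will be used for normal distributed continuous data"; the rest go to Kruskal-Wallis. The section mentions no check of equal variances and no method that lets the variance differ between arms.

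The Sample size calculation section gives the only planning data on spread, both from one earlier placebo-controlled study of domperidone after cesarean delivery: "Mean daily milk volume in the domperidone group day 4= 191.3(SD=136.1") and "Mean daily milk volume in the placebo group day4 = 91.4 (SD=60.3"). No SD is given for the tea.

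Under Randomization, "Participants will be random allocated into 3 groups with 1 : 1 : 1 ratio", with 40 per arm planned. Under Trial procedure, the tea arm is described thus: "This is an intervention arm which is designed to assess the efficacy of Wang Nam Yen herbal tea". Domperidone is the active comparator and placebo the reference.

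**The concern.** In its standard form, one-way ANOVA estimates a single residual variance from all three arms, and the Bonferroni comparisons that follow use it for every pair. This is sound when the arms have similar spread. The protocol's own figures suggest they may not: the domperidone SD is more than twice the placebo SD. The coefficients of variation are close (136.1/191.3 = 0.71 and 60.3/91.4 = 0.66), which is the pattern seen when spread grows with the mean.

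A pooled variance then sits between a large and a small one. A comparison that includes the most variable arm can get a standard error that is too small, and a comparison of the less variable arms gets one that is too large. For the tea this works in opposite directions: a difference from domperidone is declared too readily, and a moderate benefit over placebo is harder to show. A normality check does not detect the problem, because data can be normal within each arm and still differ in variance.

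**Working it through.** **Inputs.** From Sample size calculation: SD 136.1 (mean 191.3) on domperidone, SD 60.3 (mean 91.4) on placebo, 40 per arm, 15% loss. From Randomization: equal allocation. Assumed, because the protocol gives no value: tea SD, taken from 60.3 to 136.1.

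**The plan's own figure.** 3 × (1.65 + 0.84)² × 136.1² / (191.3 − 91.4)² = 34.52, as stated. Then 34.52 × 1.15 = 39.7, hence 40 per arm. After 15% loss, 40 × 0.85 = 34 remain. The calculation uses the larger SD for all arms.

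**Variance ratio.** (136.1/60.3)² = 5.09.

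**Direction.** Write sT, sD and sC for the tea, domperidone and placebo SDs and n for the arm size. The pooled standard error of any pairwise difference is √(2·MSE/n) with MSE = (sT² + sD² + sC²)/3. The correct one for arms i and j is √((si² + sj²)/n).
- Tea versus domperidone: the pooled value is too small when sT² + sD² > 2sC². Since 136.1² = 18,523 alone exceeds 2 × 60.3² = 7,272, this holds at every tea SD.
- Tea versus placebo: the pooled value is too large when sT² + sC² < 2sD², that is, sT² < 2 × 18,523 − 3,636 = 33,410, or sT < 182.8.

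**Size at 40 per arm.** Errors are simulated with normal data and no true differences (200,000 runs). The nominal rate is 5%/3 = 1.67% per pair.

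| Tea SD | Pooled SE | Correct SE, tea-domperidone (pooled/correct) | Correct SE, tea-placebo (pooled/correct) | Pooled error, tea-domperidone | Pooled error, tea-placebo | Familywise, pooled |
|---|---|---|---|---|---|---|
| 60.3 | 20.7 | 23.5 (0.88) | 13.5 (1.54) | 3.5% | 0.04% | 5.4% |
| 105.3 | 23.5 | 27.2 (0.87) | 19.2 (1.23) | 3.9% | 0.36% | 5.0% |
| 136.1 | 26.0 | 30.4 (0.86) | 23.5 (1.11) | 4.1% | 0.87% | 5.0% |

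With Welch tests at the same Bonferroni level, every pair has an error of about 1.6% to 1.7%. Results at 34 per arm are nearly the same.

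**Power for tea versus placebo at half the domperidone effect (an assumption).** The difference is 99.9/2 = 49.95, so the tea mean is 141.35. With an assumed CV of 0.69 the tea SD is 0.69 × 141.35 = 97.5. The pooled SD is √((97.5² + 136.1² + 60.3²)/3) = 102.7.

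At 34 per arm:
- Pooled SE √(2 × 102.7²/34) = 24.9; correct SE √((97.5² + 60.3²)/34) = 19.7.
- Pooled test: the critical t on 99 degrees of freedom is 2.435, so the difference must exceed 2.435 × 24.9 = 60.7. Power is roughly P(Z > (60.7 − 49.95)/19.7) = P(Z > 0.55) = 29%. Simulation gives 30%.
- Welch test: the critical t on about 55 degrees of freedom is about 2.47, so the difference must exceed 2.47 × 19.7 = 48.6. Power is roughly P(Z > (48.6 − 49.95)/19.7) = P(Z > −0.07) = 53%. Simulation also gives 53%.

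At 40 per arm, simulation gives 38% pooled and 62% Welch.

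**The case against.** **The ANOVA branch may not be used.** A normal distribution with these means and SDs would put Φ(−191.3/136.1) = 8% of domperidone volumes and Φ(−91.4/60.3) = 6% of placebo volumes below zero, so the source data were probably skewed. In simulated gamma data with these CVs, all three arms pass Shapiro-Wilk in only about 1% of trials; the rest would go to Kruskal-Wallis. This stands as a limit on the point, and it is why the figures above use normal data. It does not remove the point, because the protocol keeps ANOVA as a route for the primary outcome and that route should be valid when taken.

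**Overall error is protected.** A reader might infer from a pairwise error of 4.1% against 1.67% that the trial's false-positive rate more than doubles. The documents do not support that. The stated threshold is p < 0.05; 1.67% is only the Bonferroni share of it. If tea equals domperidone and both differ from placebo, tea versus domperidone is the only true null hypothesis, and its 4.1% is then the whole familywise error. With no differences at all, familywise error is 5.0% to 5.4%, helped by equal allocation. What remains is error spread unevenly over the pairs, and lost power.

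**The SDs describe another measurement.** They are for daily volume on day 4, whereas this trial records one timed pumping session at 72 hours. This stands too: the absolute standard errors may not transfer. The argument needs only the SD ratio, but whether that carries over is unknown.

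**This detail could sit in an SAP.** A variance check might. But the protocol itself names the comparison method, so the point concerns a stated choice rather than something left out.

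**Conclusion.** The point holds conditionally and should be acted on. If milk volume is judged normal and the planning SD ratio carries over, the pooled standard error is about 12% to 14% too small for tea versus domperidone and 11% to 54% too large for tea versus placebo, over tea SDs of 60.3 to 136.1. At half the domperidone effect, tea-placebo power falls by about 23 percentage points at 34 per arm (53% to 30%) and 24 at 40 per arm (62% to 38%).

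The directions rest only on the two planning SDs, plus a tea SD below 182.8 for the placebo comparison. The sizes rest also on the assumed tea SD, the assumed effect and normal data. Two broader conclusions do not follow: that control of error at 5% is lost, or that the primary analysis is wrong whichever branch is taken. Nor does the protocol rank the pairwise comparisons, so it cannot be said that the one losing power is the trial's designated main comparison.

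**What to change.** In the Statistical analysis section, replace the pooled-variance ANOVA comparisons with Welch ANOVA followed by separate-variance (Welch) pairwise contrasts, or with a linear model and robust standard errors. State that the Bonferroni adjustment is kept. Report each difference with a confidence interval built from its own variance, and say whether that interval is adjusted.

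The method should be fixed in advance rather than made to depend on a variance test. The change takes a line or two of text, needs no further data or participants, and costs a few degrees of freedom if the variances prove equal. It leaves the Kruskal-Wallis branch as it is. A ratio of means from a log-link model could be added in view of the similar CVs, but it is optional and not needed to repair the fault.

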**Outcome measures**

The primary outcome was breast milk volume at 72 hours after delivery. All participants were encouraged to breastfeed their infant within 24 hours of delivery based on Sanpasitthiprasong hospital's standard of care policy of early breastfeeding, frequent breastfeeding, correct positioning and avoiding the use of formula when possible. The breast milk volume was measured with a two-hour interval from last breastfeeding, using an electronic pump (Spectra S2Plus^®^, Spectra Baby USA). The electronic pump was applied for 15 minutes on each breast and the total volume of milk was recorded. Breast milk volume was also measured at 24 hours and 48 hours post-delivery. The breast milk volume at 24 hours post-delivery was used as baseline.

Secondary outcomes were observed during 72 hours after delivery period including:

(1) pregnancy outcomes such as postpartum hemorrhage, endometritis.

(2) neonatal outcomes such as neonatal jaundice, respiratory distress.
(3) adverse effects including headache, dry mouth, diarrhea, muscle cramps, itching, or allergic reactions.

(4) participant satisfaction during the three days’ postpartum period were also recorded.

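### The 72 h milk volume is compared with arm as the only factor, although pre-dose factors that may predict it are recorded: a valid test, but one that gives up an efficiency gain of unknown size

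*Protocol*

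**What the plan says.** The Outcome measures section of the protocol states: "The primary outcome was breast milk volume at 72 hours after delivery". The Statistical analysis section names the tests for continuous data: "One-way ANOVA with Bonferroni correction will be used for normal distributed continuous data", and otherwise "Kruskall-Wallis test will be used for non-normal distributed continuous data". Arm is the only factor in both, and no adjusted model appears anywhere in the protocol.

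The Trial procedure section lists the data recorded for each woman: "Obstetric data will be recorded including gestational age, numbers of pregnancy, numbers of delivery", and further on "experience of breast feeding, nurturing environment, baby birthweight". Figure 3 gives the timing as "Recording baseline data and first administration of intervention at 12-18 hours postpartum". Gestational age, parity, earlier breastfeeding experience and birthweight are fixed by delivery, so they precede treatment.

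One volume is given the name of a baseline: "The breast milk volume at 24 hours post-delivery was used as baseline". The first dose is given 12 to 18 hours after delivery, so this measurement falls 6 to 12 hours after dosing starts. The stated analysis does not use it either.

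The Randomization section describes blocks of three with no stratification. The Inclusion criteria admit deliveries from 28 to 42 weeks and do not restrict parity.

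**The concern.** The trial is small: 40 women per arm, or 34 after the stated 15% loss. The planning figures suggest wide variation between women. Gestational age, parity and birthweight are plausible predictors of early milk volume, though the protocol does not say that they are. Neither the randomisation nor the analysis takes account of them. If they are prognostic, their variance stays in the error term of every arm comparison, and any chance imbalance in them stays in the estimate. The data needed to do better are collected anyway.

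There is also a trap for anyone who adds a baseline adjustment later. The variable labelled baseline is measured after the first dose, and adjusting for it could remove part of the treatment effect.

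**Working it through.** **Inputs.** From Sample size calculation: day-4 daily volume 191.3 (SD 136.1) on domperidone and 91.4 (SD 60.3) on placebo, so the difference is 99.9 mL; 15% loss; 40 per group. Assumed here: R² of 0.05 to 0.30, and Bonferroni over three pairwise contrasts (alpha 0.05/3). The protocol gives no R².

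**The plan's own figure.** 3 × (1.65 + 0.84)² × 136.1² / 99.9² = 34.52, as stated. 34.52 × 1.15 = 39.7, rounded up to 40. Evaluable women per arm: 40 × 0.85 = 34.

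**Relative gain.** Residual SD = SD × √(1 − R²), and equivalent n per arm = 34 / (1 − R²). Neither ratio depends on the SD. The small covariate charge is left out here and included in the half-widths below.

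| Assumed R² | Interval narrower by | Equivalent n per arm |
|---|---|---|
| 0.05 | 2.5% | 35.8 |
| 0.10 | 5.1% | 37.8 |
| 0.20 | 10.6% | 42.5 |
| 0.30 | 16.3% | 48.6 |

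**Break-even.** With N = 3 × 34 = 102 and three covariates, the residual degrees of freedom are 102 − 3 − 3 = 96. The expected variance inflation from estimating the covariate effects is about 1 + 3/(96 − 1) = 1.0316. Adjustment pays once 1 − R² < 1/1.0316, that is, once R² exceeds about 0.03.

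**Illustrative power.** Two-sample noncentral t, difference 99.9 mL, 34 per arm, alpha 0.05/3, no covariate charge. The SD is taken in two ways: 136.1 in both arms, as the sample size formula does, or the two stated SDs combined, √((136.1² + 60.3²)/2) = 105.3.

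| R² | Power, SD 136.1 | Power, SD 105.3 |
|---|---|---|
| 0 (unadjusted) | 71.4% | 92.4% |
| 0.05 | 74.0% | 93.7% |
| 0.10 | 76.6% | 95.0% |
| 0.20 | 82.0% | 97.0% |
| 0.30 | 87.4% | 98.5% |

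**Illustrative 95% half-width, SD 136.1.** Unadjusted: SE = 136.1 × √(2/34) = 33.01; times t(99) = 1.984 gives 65.5 mL. With three covariates: SE = 33.01 × √(1 − R²) × √1.0316; times t(96) = 1.985 gives 64.9, 63.1, 59.5 and 55.7 mL at R² of 0.05, 0.10, 0.20 and 0.30. These half-widths are not Bonferroni-adjusted.

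The power and mL figures are illustrations only. The planning SDs describe a day's volume on day 4, whereas the primary outcome is one pump session, 15 minutes per breast, at 72 hours.

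**The case against.** The strongest reply is that nothing here is an error. One-way ANOVA and Kruskal-Wallis are legitimate comparisons of randomised arms, the protocol promises no adjustment, and covariates are often settled in an analysis plan that is not at hand. The first part stands in full. A reader might infer that the unadjusted comparison is biased or has the wrong error rate; the documents do not support that, because allocation is randomised. The last part stands only partly. The protocol does not leave the method open: it names the tests, and Kruskal-Wallis cannot take covariates.

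The second reply is that the benefit is conjecture. This also stands: no R², correlation or statement of prognostic value appears anywhere. At an R² of 0.05 the gain is one to three points of power. Excluding mothers of sick, separated neonates may also thin the preterm end, so the spread in gestational age may be narrower than 28 to 42 weeks suggests; the distribution is not given.

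The third reply concerns the SD. A reader might infer from the 136.1 figures that the trial is short of power without adjustment. That does not follow. With the two stated SDs combined, unadjusted power for 99.9 mL is already about 92%, and the gain shrinks to between 1 and 6 points. The gain would then matter mainly for smaller differences. Tea against domperidone could be one, but the protocol gives no expected difference for it.

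**Conclusion.** The point holds as a missed efficiency gain of unknown size. The protocol fixes an analysis with arm as the only factor while collecting pre-dose factors that plausibly predict the outcome, under unstratified randomisation with about 34 evaluable women per arm. The planned test remains valid.

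The firmest measure of size is the factor 1/(1 − R²), which does not depend on the planning SDs. It runs from about 36 to 49 equivalent women per arm over the assumed range. If R² is below about 0.03, nothing is gained. Adjustment deals with chance imbalance only in the factors that are modelled. It would be too strong to say that precision is known to be thrown away, since that would require evidence that these factors are prognostic in this population.

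**What to change.** Before unblinding, state the primary analysis as a linear model of 72 h volume in mL on arm, gestational age, parity (number of deliveries) and birthweight. Use heteroscedasticity-robust standard errors, and report Bonferroni-adjusted pairwise contrasts with confidence intervals. Fix one covariate list and one scale now, so that neither is chosen after seeing the data. Staying in mL avoids taking the log of a zero yield, and robust errors suit the unequal SDs that the protocol cites.

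State that the 24 h volume is not a covariate. Exclude likewise any other item that may be recorded after the first dose, such as fluid intake and output or neonatal complications. Keep the planned ANOVA or Kruskal-Wallis comparison as a sensitivity analysis.

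The cost is a few sentences and three degrees of freedom, with no new data. The downside is a negligible gain, or a very slight loss below the break-even R², if the covariates turn out not to be prognostic.

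### A normality check picks the primary test, and the branch it is likely to pick stops at a global Kruskal-Wallis test that cannot show whether the tea works

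*Protocol*

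**What the plan says.** The primary outcome is a single continuous measure: "The primary outcome was breast milk volume at 72 hours after delivery" (Protocol, Outcome measures). The Statistical analysis section has no separate rule for it, so it follows the general rule for continuous data.

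- **Choice of test.** "Continuous data will be assessed for normal distribution using histogram and Shapiro–Wilk test". No threshold is given, nor a rule for when the histogram and the test disagree. The section does not say whether the check is made per arm, on pooled data or on residuals.
- **Normal branch.** One-way ANOVA with Bonferroni correction.
- **Non-normal branch.** "Kruskall-Wallis test will be used for non-normal distributed continuous data". No pairwise test and no correction are named.

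The Trial procedure section states what the tea arm is for: "This is an intervention arm which is designed to assess the efficacy of Wang Nam Yen herbal tea". It describes the double-placebo arm as the reference and domperidone as the active comparator. No section names tea versus placebo as the primary contrast.

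**The concern.** With three arms, a global test asks only whether the arms differ somewhere. One of the arms is an active drug that the sample size calculation expects to roughly double milk volume. A significant global result may therefore reflect domperidone alone.

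On the ANOVA branch, Bonferroni supplies the missing step. On the Kruskal-Wallis branch nothing does, and milk volume is bounded at zero with a large SD, so this is the branch one would expect to reach. Whether the trial yields a stated test of its own question then depends on a normality check with no decision rule, made once the data are in hand.

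**Working it through.** **Inputs (Protocol, Sample size calculation).** "Mean daily milk volume in the domperidone group day 4= 191.3(SD=136.1") and "Mean daily milk volume in the placebo group day4 = 91.4 (SD=60.3"). Planned size is 40 per arm with 15% loss.

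**The plan's own figure.** 3 × (1.65 + 0.84)² × 136.1² / (191.3 − 91.4)² = 3 × 6.2001 × 18523.21 / 9980.01 = 34.52, as stated. 34.52 × 1.15 = 39.7, hence 40 per arm; 40 × 0.85 = 34 evaluable. The checks below use 34 and 40 per arm.

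**Are the planning values compatible with normal data?**
- CV: 136.1/191.3 = 0.71 (domperidone); 60.3/91.4 = 0.66 (placebo).
- Distance of zero from the mean: 191.3/136.1 = 1.41 SD; 91.4/60.3 = 1.52 SD.
- A normal distribution would put Φ(−1.41) = 8.0% and Φ(−1.52) = 6.5% of volumes below zero, which is impossible. Right skew is likely, though its form is not known.

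**Which branch is reached, and what does its test show?** Three arms were simulated, 2,000 trials per scenario, using the planning means and SDs (before censoring, for the zero-censored normal). The distributional shapes are assumptions. Shapiro-Wilk was applied at 0.05 in each arm; the second column gives the proportion of trials with a rejection in at least one arm, with the tea equal to either domperidone or placebo. The third column sets the tea equal to placebo, with domperidone working as assumed.

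| Assumed shape | Shapiro-Wilk rejects in at least one arm | Kruskal-Wallis p < 0.05, tea equal to placebo |
|---|---|---|
| Gamma | 99–100% | 97–99% |
| Lognormal | 100% | 100% |
| Weibull | 98–99% | 96–98% |
| Zero-truncated normal, matched to mean and SD | 89–96% | 92–96% |
| Zero-censored normal | 38–51% | 96–98% |
| Exactly normal | 14–15% | 96–98% |

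If the check is run on pooled data, it rejects in essentially every trial for all shapes except the exactly normal one (53–97%), because differences between arms alone break normality.

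**If the 72-hour volume is less variable than planned** (gamma, equal arms, 40 per arm), the any-arm rejection rate is 93% at CV 0.5, 78% at 0.4 and 58% at 0.3.

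**If domperidone does less than planned** (gamma, tea equal to placebo, 34 per arm), Kruskal-Wallis is significant in about 66% of trials when domperidone raises volume 1.5-fold and in about 24% when it raises it 1.25-fold. Both effects are assumptions.

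**What a pairwise test adds.** With the tea equal to placebo and domperidone working as assumed, a tea-placebo Mann-Whitney test at 0.05, done only after a significant Kruskal-Wallis test, is falsely positive in 5.5% (34 per arm) and 5.0% (40 per arm) of trials. The global test is significant in 97–99% of the same kind of trial. The missing contrast is what separates the two.

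**The case against.** Four objections deserve an answer.

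**The plan does test tea against placebo.** A reader might infer that it never does. The text does not support that: Bonferroni after ANOVA implies pairwise comparisons, and with three arms tea versus placebo is one of them. The defect is confined to the Kruskal-Wallis branch.

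**The branch is not certain.** A reader might also infer that the data must be skewed and that the rank branch is all but guaranteed. That goes too far. The planning SDs are for daily volume on day 4 in another study, whereas the outcome here comes from one session: "The electronic pump was applied for 15 minutes on each breast". Nothing shows that the CV carries over. The any-arm rule is an assumption, and a histogram is consulted too. Under normal or nearly normal data the per-arm rejection rate is 14–51%. This objection stands and limits the claim to a likely branch.

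**Ordinary follow-up would be safe.** A reader might fear a family-wise error near 12% from pairwise tests added later. That figure applies only to three unadjusted tests run without a gate (about 12–13% under the global null). With exactly three arms, tests done only after a significant Kruskal-Wallis result hold about 5% (5.5% and 4.8%). So inflation is not a harm that follows from the plan. But the protocol specifies neither procedure.

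**The follow-up test is detail for an SAP.** An SAP may exist, and nothing forbids a pairwise follow-up. This would settle the matter had the protocol left the method open. It did not: it fixes both branches and gives pairwise handling to one only.

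**Conclusion.** The point holds for the Kruskal-Wallis branch. The protocol lets the data choose the primary test without a decision rule, and on the non-normal branch it specifies only a global test. If 72-hour volumes are about as variable and right-skewed as the planning values suggest, that branch is reached in roughly 89–100% of trials on a per-arm check. If domperidone also works as assumed, the global test is significant in 92–100% of trials across the shapes tried (about 97–99% for gamma) with an inert tea. On that branch the plan as written does not answer whether the tea works.

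Three assumptions carry the size of this: the right-skewed shape, the transfer of the day-4 daily CV to a single pumping session, and a domperidone effect of the planned size. Weaker versions lower the percentages. They do not change the fact that this branch contains no tea-placebo contrast.

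**What to change.** In the Statistical analysis section:

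1. Remove the normality-test switch for the primary outcome.
2. Name tea minus placebo in 72-hour volume as the primary contrast, estimated with a 95% CI by one prespecified method that allows unequal variances, such as a Welch or robust-standard-error comparison. The planning SDs differ by a factor of 136.1/60.3 = 2.3, so equal variances should not be assumed.
3. Give the Mann-Whitney test as sensitivity analysis.
4. State one multiplicity rule for the two remaining pairs.

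If the rank route is kept instead, state that tea versus placebo is tested pairwise on that branch under the same multiplicity rule as on the ANOVA branch.

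The cost is a few sentences and no added data. If the tea effect equals the planned domperidone effect, a two-sided 5% comparison with SD 136.1 in both arms has about 86% power at 34 per arm and 91% at 40. At 0.05/3 these become 74% and 81%. A Mann-Whitney test at 0.05/3, with gamma data and each arm's own SD, has about 91% and 96%. If tea versus placebo is the single primary contrast at 5%, no larger sample is needed on these assumptions. If it shares a Bonferroni correction, power at 34 evaluable per arm falls somewhat below 80% on the more cautious calculation.
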